### Antistigma Campaign Evaluation

Data from the baseline and follow-up study surveys will be used to assess whether there were improvements among young transgender women in (1) feeling of safety in health clinics; (2) perceptions of provider, staff, and other patient attitudes toward transgender women; (3) anticipated stigma; (4) medical mistrust; (5) health care participation; and (6) avoidance of health care. We will use repeated measures ANOVA to compare changes in mean stigma scores over the course of time in participating in the intervention (ie, before and after the intervention). In intent-to-treat analyses, we will use generalized estimating equations (GEE) Poisson or negative binomial models with robust SEs to compute the ratio of the single arm intervention rates of change in the mean value of stigma over the study period. GEE methods produce estimates that account for within-subject correlation of stigma scores across time [53]. GEE methods will also be used to assess whether changes in stigma are associated with changes in PrEP uptake and adherence and HIV care linkage over time.

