### Sample Size and Power Calculation

We propose to enroll 150 participants and have estimated 80% power to detect effects for our primary outcomes using formulas for longitudinal study designs with attrition. These estimates account for an expected attrition of 15% of the sample by 12 months, as well as adjustment for time-dependent covariates in longitudinal analysis. We will also have 80% power to detect correlations of 0.23 of continuous baseline covariates with baseline responses and changes in study responses from baseline to 6 months.

In the analysis of changes, we will have 80% power in 2-sided tests with a type I error rate of 5% to detect changes from baseline to 12 months of 0.41 to 0.53 SDs in continuous responses, depending on within-subject correlation of the response, and increases of 10-15 percentage points in the frequency of binary responses, depending on baseline frequency as well as within-subject correlation. Thus, this study is powered to detect small to medium effect sizes that are consistent with or smaller than others reported in the literature.

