### Missing Data

Missing items at any visit should be minimal owing to the electronic data collection protocol described above. However, some loss to follow-up is inevitable. To assess sensitivity to dropout, multiple imputation will be used, under both the standard conditionally missing-at-random assumption, as well as plausible missing not-at-random scenarios. GEE methods can also be weighted to handle missing data.

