## Results

Between the study pilot and the study intervention, the COVID-19 pandemic emerged, which caused a substantial impact on the implementation of the study. Study recruitment began in February 2022, initially slowly as Brazil was still facing high numbers of COVID-19 cases and deaths. Nevertheless, we were able to complete study enrollment by early July 2022. To achieve that, we combined prior experience of both the US and the Brazilian teams with transgender communities to new recruitment strategies. The team uses dynamic and multifaceted approaches to community engagement strategies to enhance existing strategies and implement new strategies using field and digital media initiatives for recruitment. The team also encouraged participants to bring other individuals and gave them gifts or reimbursement (eg, peer referrals).

Recruiting and retaining transgender women who are young, early in their gender development, marginalized, and less connected within community poses significant challenges to engagement in the intervention and retention. Therefore, the study team currently has a major focus on retention. Strong supervised peer navigation is important to reach, engage, and retain young transgender women. Regular and meaningful engagement with the community is essential to maintain these connections. Furthermore, we have been providing cell phone credits to the participants retained in the intervention. In addition, we also give participants small gifts, such as study bags, sponge bags, and daily planners, among others, if they achieve some goals (eg, attending study visits in the study window). In addition, we will also conduct raffles of electronic items (such as portable cell phone chargers and earphones) for participants completing the intervention and study visits. Peer navigators also maintain close connections with participants, supporting them in their in-person and remote interactions. Future perspectives are to complete follow-up with study participants by July 2023 and to analyze study data and disseminate intervention results December 2023.

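### The stigma analysis relies on repeated measures ANOVA and on GEE with optional weighting; a mixed model on all visits would handle the expected dropout better, at a modest gain

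*Protocol article*

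**What the plan says.** The section Antistigma Campaign Evaluation names two analyses of stigma scores. The first is ANOVA: "We will use repeated measures ANOVA to compare changes in mean stigma scores over the course of time in participating in the intervention". The parenthesis after those words equates the comparison with before and after the intervention. The second, placed under intent-to-treat, is GEE: "we will use generalized estimating equations (GEE) Poisson or negative binomial models with robust SEs". GEE is also to relate changes in stigma to changes in PrEP uptake, adherence and care linkage. Neither analysis is called the main one.

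The section Missing Data sets the role of the dropout methods. To assess sensitivity to dropout, "multiple imputation will be used, under both the standard conditionally missing-at-random assumption", and also under "plausible missing not-at-random scenarios". On weighting it says only that "GEE methods can also be weighted to handle missing data".

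The section Sample Size and Power Calculation gives the scale: "We propose to enroll 150 participants", with an "expected attrition of 15% of the sample by 12 months". The Results section says that recruiting and retaining this population "poses significant challenges to engagement in the intervention and retention". Stigma is measured at baseline and at weeks 12, 24, 36 and 48.

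**The concern.** Classical repeated measures ANOVA needs a complete record for every participant it uses. Unweighted GEE is valid in general only if dropout is completely at random or depends only on covariates in the model. The article gives reason to doubt that. Its Introduction links stigma and anticipated discrimination to underuse and postponement of care, and the follow-up visits take place in person at a health institution. Stigma-related dropout is therefore plausible, although the article does not report it.

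If participants with higher stigma leave, the mean of those still attending can fall with no true change. That is the direction the Discussion expects. The study has one arm, and the external comparison focuses on PrEP and ART adherence and viral suppression, so no control series exists for stigma. Addressing stigma is the first stated objective, although stigma is not among the primary outcomes listed in the abstract.

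**Working it through.** **Inputs from the article.** 150 enrolled; 15% attrition by 12 months; five visits; 2-sided 5% test; 80% power; stated detectable change 0.41 to 0.53 SD.

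**Assumptions, not in the article.** Within-person correlation ρ = 0.5; normal scores on an identity scale; 5% of the three intermediate visits missed; log-odds of dropout rising by 0.7 to 1.4 per SD of the previous score; no true change.

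**1. The stated detectable change.** The plain one-group formula is d = (1.960 + 0.842) × √(2(1 − ρ)/n). With n = 150 × 0.85, about 127, it gives 2.802 × √(2/127) = 0.35 SD at ρ = 0 and 2.802 × √(1/127) = 0.25 SD at ρ = 0.5. The stated 0.41 to 0.53 SD is not reproduced; it is the more conservative figure. The article says it adjusts for time-dependent covariates but gives neither that adjustment nor ρ, so this is not called an error. The range serves below only as a yardstick.

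**2. Records kept by ANOVA.**
- Baseline and week 12 only: dropout per interval is 1 − 0.85^(1/4) = 0.040, so 150 × 0.960 × 0.95 ≈ 137.
- Baseline and week 48 only: 150 × 0.85 = 127.5.
- All five visits: 150 × 0.85 × 0.95³ = 109.3.

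**3. Precision.** The variance of a complete-case change is 2(1 − ρ)/n in SD² units.
- n = 127.5: 1/127.5 = 0.00784, SE 0.089.
- n = 109.3: 1/109.3 = 0.00915, SE 0.096.
- A likelihood-type fit to all observed visits had a simulated SE of about 0.085. The simulated variance ratio was about 1.05 for the baseline/week-48 contrast.
- For five visits this implies (127.5/109.3) × 1.05 = 1.17 × 1.05 = 1.22. Simulations mostly gave 1.2 to 1.25. One gave (0.097/0.085)² = 1.30, but with only 150 mixed-model fits.

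**4. False change at week 48 with no true change.** Dropout depends on the previous score, 15% by week 48, 5% intermittent misses, 3,000 simulated trials per row:

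| Dropout log-odds per SD | Complete-case ANOVA, five visits | GEE, independence | Likelihood-type fit, true exchangeable correlation |
|---|---|---|---|
| 0.7 | +0.014 | −0.052 | +0.001 |
| 1.0 | +0.017 | −0.075 | −0.002 |
| 1.4 | +0.022 | −0.097 | −0.002 |

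Separate runs of the independence version gave −0.053 to −0.056, −0.071 to −0.075 and −0.087 to −0.099 in the three rows. Unweighted GEE with the true exchangeable correlation supplied gave +0.003, −0.002 and −0.016. A fitted mixed model gave −0.008 at log-odds 1.0.

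**5. Effect on the test.** For independence GEE with an SE of about 0.088, a bias of 0.053 is 0.60 SE, so the rejection rate is P(Z > 1.36) + P(Z < −2.56) ≈ 9%. A bias of 0.073 is 0.83 SE, which gives about 13%. Simulation with dropout alone gave 9% and 14% at log-odds 0.7 and 1.0.

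**6. If dropout depends on the unseen score** (log-odds 0.7 to 1.0): independence GEE −0.07 to −0.09 SD (rejection 11 to 17%), complete-case change −0.01 to −0.02, imputation under missing at random −0.03 to −0.04. No method valid only under missing at random removes this, so the planned missing-not-at-random scenarios are still needed.

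**7. Against the yardstick.** 0.05/0.53 = 9% and 0.09/0.41 = 22% of the stated detectable change. Against the plain 0.25 SD from step 1, 0.09 is 36%.

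**The case against.** The strongest reply has four parts.

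- The plan does commit to multiple imputation, under missing at random and under missing-not-at-random scenarios, for the purpose of examining dropout. A reader might infer that optional weighting is the only safeguard, or that nothing in a single-arm study would expose a false fall. The Missing Data section contradicts both. This part stands in full.
- The ANOVA may be a two-point contrast, since the article equates it with before and after the intervention. Intermediate misses then do not matter, and the loss of precision is about 5%. This stands as one natural reading; the wording does not settle it.
- A reader might infer that dropout makes both analyses show a false reduction. It does not. Complete-case ANOVA was nearly unbiased and, with dropout depending on earlier scores, erred slightly upward. The GEE bias belongs to the independence working correlation, and the article names no structure. This stands too, although the exchangeable result needs the correlation to be right.
- An article may leave the working correlation, the handling of incomplete records and the choice of leading model to an analysis plan that is not shown. This stands for those details. It does not cover what the article itself fixes: ANOVA as a named method, imputation as sensitivity only, and weighting as optional.

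**Conclusion.** The point holds as a modest improvement to the stigma analysis. As written, neither named method carries a committed adjustment for the expected attrition, and a better method is available at almost no cost.

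For ANOVA the price is precision: about 5% more variance on the baseline/week-48 reading, and about 20 to 30% more on the five-visit reading, which depends on the assumed 5% of missed intermediate visits. For GEE the risk is a false fall of about 0.05 to 0.09 SD (just under 0.10 in some runs at the steepest slope). It arises only if higher-stigma participants leave and an independence working correlation is used. The dropout slopes, ρ = 0.5 and normal scores are assumptions. A bias of this size could not by itself produce a change as large as the study says it can detect, but it could raise the false-positive rate above 5%.

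The documents do not support a stronger conclusion, namely that the planned stigma result would be spurious or that dropout bias would go unseen.

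**What to change.** Replace repeated measures ANOVA with one likelihood-based linear mixed model on all observed visits, with visit as a category, and name it as the main stigma analysis. It is valid under missing at random and uses partial records. Where GEE is kept, including for the link between stigma and PrEP or care outcomes, make the main version either inverse-probability weighted, with weights built from earlier visits, or based on imputation under missing at random. State the working correlation. Keep the planned missing-not-at-random imputation as sensitivity, and say that it covers the stigma scores.

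The change is to analysis wording only and needs no new data. It costs slightly more analysis work and, for the weighted version, reliance on a dropout model.

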### Sample Size and Power Calculation

We propose to enroll 150 participants and have estimated 80% power to detect effects for our primary outcomes using formulas for longitudinal study designs with attrition. These estimates account for an expected attrition of 15% of the sample by 12 months, as well as adjustment for time-dependent covariates in longitudinal analysis. We will also have 80% power to detect correlations of 0.23 of continuous baseline covariates with baseline responses and changes in study responses from baseline to 6 months.

In the analysis of changes, we will have 80% power in 2-sided tests with a type I error rate of 5% to detect changes from baseline to 12 months of 0.41 to 0.53 SDs in continuous responses, depending on within-subject correlation of the response, and increases of 10-15 percentage points in the frequency of binary responses, depending on baseline frequency as well as within-subject correlation. Thus, this study is powered to detect small to medium effect sizes that are consistent with or smaller than others reported in the literature.

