**Methods:**

The *Brilhar e Transcender* (BeT) study is a status-neutral, peer-led, single-arm digital intervention study enrolling 150 young transgender women in Rio de Janeiro, Brazil. The intervention was pilot tested and refined using data from a formative phase. The BeT intervention takes place over 3 months, is delivered remotely via mobile phone and in person by peers, and comprises three components: (1) BeT sessions, (2) digital interactions, and (3) automated messages. Eligibility criteria include identifying as transgender women, being aged 18-24 years, speaking in Portuguese, and living in the Rio de Janeiro metropolitan area in Brazil. The primary outcomes are HIV incidence, pre-exposure prophylaxis uptake, linkage to HIV care, and viral suppression. Primary outcomes were assessed at baseline and quarterly for 12 months. Participants respond to interviewer-based surveys and receive tests for HIV and sexually transmitted infections.

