## Introduction

Efforts to end the HIV epidemic by 2030 will not be possible without enhanced efforts to prevent new infections among youths and young adults [1]. Despite the availability of effective HIV care and prevention interventions, reductions in HIV prevalence have stalled, in part, owing to the lack of progress in reducing new infections among youths, especially those in low- and middle-income countries (LMICs) where most new infections are acquired. Innovations in HIV interventions have also failed to adequately reach marginalized populations most affected by HIV [2]. Transgender women are one of the most severely affected populations by HIV worldwide [3]. Brazil has a concentrated HIV epidemic with a 0.4% prevalence in the general population [4] with over 900,000 people living with HIV in the country [5] and the highest prevalence among transgender women who have sex with men [6,7]. Within the population of transgender women, young transgender women are at high risk for HIV and poor HIV care outcomes. The first respondent-driven sampling-based study of HIV risk and pre-exposure prophylaxis (PrEP) awareness among Brazilian transgender women identified that 24.2% of youths aged 18-24 years were living with HIV. Young transgender women also had lower knowledge of HIV prevention strategies (including PrEP) and higher HIV risk than their older peers, with 3 times as many unrecognized infections than adults [8]. These findings are worse than those reported in prior research, suggesting that 1 in 5 young transgender women were infected with HIV before having been aged 25 years [9,10].

Global data reflect a lack of incident infection decline among youths and point to a need for early intervention to curb risk among young transgender women [11]. In a study conducted from 2018 to 2020 using the Limiting Avidity assay as part of a recent infection testing algorithm, the annualized HIV incidence rate was 7% overall and 9% among transgender women [12]. In the largest PrEP demonstration study in Latin America, which enrolled a total of 9509 people, young and transgender participants had lower odds of long-term engagement in PrEP [13].

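### The 80% power claim for the primary outcomes takes in HIV incidence, but the only binary effect given cannot apply to new infections

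*Protocol article*

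**What the plan says.** The Abstract (Methods) states: "The primary outcomes are HIV incidence, pre-exposure prophylaxis uptake, linkage to HIV care, and viral suppression". Study Procedures and Measures again puts HIV incidence first among the outcomes collected at follow-up.

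Sample Size and Power Calculation proposes 150 participants and says the authors "have estimated 80% power to detect effects for our primary outcomes using formulas for longitudinal study designs with attrition". It makes no exception for any primary outcome. On dropout it adds: "These estimates account for an expected attrition of 15% of the sample by 12 months". The effects it then quantifies, at 80% power and a two-sided 5% level, are changes from baseline to 12 months: 0.41 to 0.53 SD for continuous responses and, for binary ones, "increases of 10-15 percentage points in the frequency of binary responses, depending on baseline frequency as well as within-subject correlation". It also gives a detectable correlation of 0.23. It gives no incidence rate, person-years, expected events, comparator rate or target reduction.

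Statistical Analysis is narrower. Its primary endpoint and primary hypothesis concern PrEP uptake and adherence and HIV care linkage, before versus after the intervention. Its external comparison concerns PrEP and ART adherence and viral suppression. Neither part names HIV incidence.

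The only incidence rates in the article are background figures in the Introduction: "the annualized HIV incidence rate was 7% overall and 9% among transgender women".

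**The concern.** Read together, the Abstract and the power section promise 80% power for HIV incidence. The effect size offered in support is a rise in a frequency that is present at baseline and measured again in the same people. A new-infection rate has no such baseline frequency, so the promise has no visible basis for this outcome.

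This matters for how a null result would be read. With roughly 9 to 14 seroconversions expected if the intervention did nothing, even a large true reduction could easily go undetected. A reader who trusts the 80% figure could then take an unchanged rate as evidence that the intervention does not prevent infection.

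**Working it through.** **Step 1: the plan's own binary figure.** Inputs from the power section: 150 enrolled and 15% attrition, so 150 × 0.85 = 127.5, about 127 pairs; two-sided 5%; 80% power. For a paired comparison with baseline proportion p0, follow-up proportion p1 = p0 + d, within-subject correlation φ, and discordant proportion D = p0 + p1 − 2[p0·p1 + φ√(p0(1−p0)p1(1−p1))], the detectable d solves

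d√n = 1.96√D + 0.84√(D − d²).

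At n = 127:

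| Baseline | φ | Detectable increase |
|---|---|---|
| 5% | 0.6 | 6.5 points |
| 10% | 0.4 | 10.0 points |
| 30% | 0.2 | 15.4 points |
| 50% | 0 | 17.4 points |

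The printed 10 to 15 points is compatible with such a calculation. The article states neither the baseline frequency nor the correlation, so the figure cannot be reproduced uniquely and the formula actually used is not known.

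**Step 2: can that effect describe HIV incidence?**

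- *Baseline.* Follow-up HIV testing is confined to HIV-negative participants (Laboratory Assessments and Clinical Approach). Among those at risk the baseline frequency is zero by definition, and there is no within-subject correlation to enter.
- *Direction.* The stated effect is an increase. Benefit on incidence is a decrease.
- *Size.* At 9 per 100 person-years the 12-month risk is about 9% (1 − e^(−0.09) = 8.6%). Preventing every infection would lower it by about 9 points, less than the smallest stated detectable change of 10.

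The first two points need no assumption about test, effect or HIV-status mix. The third needs only the Introduction's rate.

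**Step 3: illustration of scale.** The article gives no incidence effect, so the following are assumptions of this review: a one-sample exact Poisson test against 9 per 100 person-years treated as known, the two-sided 5% level taken as 2.5% in the lower tail, and a true halving. The null mean is μ0 = 0.09 × person-years. The cutoff c is the largest count with P(X ≤ c | μ0) ≤ 0.025, and power is P(X ≤ c | μ0/2).

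The person-years run from all 150 HIV-negative with no dropout to an assumed 24.2% HIV-positive at entry (the Introduction's survey figure, not a figure for this cohort), with linear 15% attrition (average retention 0.925) over 48 weeks: 150 × 0.758 × 0.925 × 48/52 = 97.1.

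| Scenario | Person-years | μ0 | c | Power for a halving |
|---|---|---|---|---|
| All negative, no dropout, 1 year | 150 | 13.5 | 6 | 48.8% |
| All negative, attrition, 48 weeks | 128.1 | 11.5 | 4 | 31.8% |
| 24.2% positive, attrition, 1 year | 105.2 | 9.5 | 3 | 30.5% |
| 24.2% positive, attrition, 48 weeks | 97.1 | 8.7 | 2 | 18.9% |

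Because counts are whole numbers, power moves in steps. At 97.3 person-years P(X ≤ 3) = 0.0252, so c = 2 and power is 18.8%; at 97.5 it is 0.0249, so c = 3 and power is 36.2%. Between about 97 and 128 person-years, roughly 20-40% is as precise as the result deserves. The steps also mean that 150 person-years is not quite the peak: c = 6 first becomes available at μ0 = 13.06 (145.1 person-years), where P(X ≤ 6 | 6.53) = 52%.

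With 150 person-years, 80% power needs a rate ratio of 0.35 (P(X ≤ 6 | 4.73) = 0.80), a 65% reduction.

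Other tests give the same message. Over 97 to 150 person-years, score, log and square-root approximations and a two-equal-group comparison give 22-58%; a one-sided exact 5% test gives about 36-64%. By the score formula a halving needs [(1.96√0.09 + 0.84√0.045)/0.045]² ≈ 290 person-years.

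**Step 4: precision.** Nine events in about 97 person-years give 9.3 per 100 person-years, with an exact 95% CI of 4.2 to 17.6.

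**The case against.** The strongest reply is that no incidence test is planned. Statistical Analysis confines the primary hypothesis to PrEP uptake and adherence and care linkage, so the power sentence may have been meant only for those. The Poisson test, the halving and the fixed 9% are assumptions of this review. That stands, and it rules out the stronger reading that a stated incidence calculation is wrong, because none is printed. It does not remove the problem: as worded, the Abstract and the power section still attach 80% power to incidence, and a reader cannot tell that a narrower set was intended.

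The 9% is also background, not specific to ages 18-24, and enrolment favours people with a PrEP indication who are not using it, so this cohort's rate could be higher. That too stands. But the score requirement of 290 person-years at 9% corresponds to about 26 expected events (290 × 0.09), and 150 person-years would need a rate near 17 per 100 to supply them.

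Three further inferences are tempting and not supported:

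- A single low figure such as 19% should not be quoted as the study's power. It depends on which side of a discrete step an assumed follow-up time falls.
- The 10 to 15 points cannot be said to come from a paired formula; it is only compatible with one.
- The cost per infection averted is not shown to rest on this study's own rate. Statistical Analysis calls that estimate rough and bases it on Brazilian cohort data on incidence and care outcomes.

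Finally, an article may leave the detail of an incidence analysis to the full protocol. The point here is a printed claim that is too broad, not missing detail.

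**Conclusion.** The concern holds as a matter of scope. The article claims 80% power for its primary outcomes, lists HIV incidence among them, and supports the claim for binary outcomes only with an effect that cannot apply to new infections. That conclusion rests on the text alone.

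The size of the gap is illustrative. Against a fixed 9 per 100 person-years, power for a halving is about 49% with the whole cohort HIV-negative and fully followed, and stays at or below about 52% anywhere from 97 to 150 person-years. Every alternative test tried also stays below 80%. The result depends on the 9% rate, the halving and, below 150 person-years, the assumed attrition, follow-up and HIV-positive share. More HIV-positive participants would lower it further: at an assumed 50%, exact power is about 15-22%.

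This says nothing against the power for PrEP uptake and adherence or care linkage.

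**What to change.** - Restrict the 80% power sentence to the outcomes analysed as change from baseline, naming them: PrEP uptake and adherence, and HIV care linkage, as in Statistical Analysis.
- Reconcile the primary outcomes in the Abstract, Statistical Analysis and the power section.
- State that the study is not powered for HIV incidence, that incidence will be reported as a rate with an exact 95% CI, and that an unchanged or non-significant rate will not be taken to show absence of a preventive effect. Giving the expected width, as in the example of about 4 to 18 per 100 person-years, would help the reader.

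The cost is wording in the abstract, sample-size and analysis sections. No participants, visits or procedures are added. The downside is a less favourable power statement for one primary outcome.

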### Study Procedures and Measures

Table 1 describes the study procedures. Potential participants are recruited by a community education team, through word of mouth, and via referrals from enrolled participants. Recruitment also occurs at the HIV prevention services based at our site and at an on-site mobile legal unit that offers weekly access to free legal services for transgender people.

Participants have 5 in-person encounters at the National Institute of Infectious Diseases Evandro Chagas, Fiocruz, including a screening and enrollment visit followed by 4 quarterly visits (at weeks 12, 24, 36, and 48). The BeT intervention takes place between the enrollment visit and the 12-week visit and is completed within that time frame. Trained staff conduct interviewer-administered surveys to participants at all study visits.

At baseline, all participants respond to a screening questionnaire and demographic information, after signing the written informed consent form. Baseline and quarterly survey content build upon questionnaires previously developed and tested with transgender women in Brazil and in the United States, as described in Table 2. During follow-up visits, we will collect information on study outcomes: HIV incidence, PrEP uptake and adherence among HIV-negative participants, and linkage to HIV care and viral load suppression among those living with HIV. In addition, we will also collect data on implementation science outcomes: (1) maintenance (pre- and poststudy) for study coordination, feasibility (poststudy) for peer health navigators, and feasibility, acceptability, and appropriateness (poststudy) for study participants.

**Table 1 table1:** Measures of the *Brilhar e Transcender* study.

Measures		Time frame	Source
Demographics		Baseline	Grinsztejn et al [6]
Transitioning process		Baseline and quarterly	Grinsztejn et al [6]
Food insecurity		Baseline and quarterly	Adapted from the Food and Agriculture Organization of the United Nations [35]

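### The 80% power claim for 10-15 point increases is worked on the whole sample, but linkage and viral suppression apply only to participants living with HIV and HIV incidence is not covered by any stated figure

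*Protocol article*

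**What the plan says.** The abstract describes a "status-neutral, peer-led, single-arm digital intervention study enrolling 150 young transgender women" and names four primary outcomes: HIV incidence, PrEP uptake, linkage to HIV care and viral suppression.

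Sample Size and Power Calculation states: "We propose to enroll 150 participants and have estimated 80% power to detect effects for our primary outcomes". On losses it adds: "These estimates account for an expected attrition of 15% of the sample by 12 months". It also says that the estimates allow for adjustment for time-dependent covariates, without giving a size. For two-sided 5% tests it then lists as detectable "changes from baseline to 12 months of 0.41 to 0.53 SDs in continuous responses" and "increases of 10-15 percentage points in the frequency of binary responses, depending on baseline frequency as well as within-subject correlation".

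Study Procedures and Measures assigns the outcomes to strata: "HIV incidence, PrEP uptake and adherence among HIV-negative participants, and linkage to HIV care and viral load suppression among those living with HIV". Incidence can arise only in participants who are HIV-negative at entry.

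Eligibility Criteria require HIV-negative participants not to be using PrEP. Those living with HIV must be off ART, or have a detectable viral load and not be linked to care. The article plans no HIV-status split. Its only related figure, from a survey cited in the Introduction, is that "24.2% of youths aged 18-24 years were living with HIV".

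**The concern.** The power statement speaks of the primary outcomes together and starts from all 150, yet none of the four is measured on all 150. Two belong to what may be the much smaller stratum. If the 10-15 point figure describes the whole sample, it overstates what the study can detect for linkage and viral suppression. A modest or null change among participants living with HIV could then be reported as a finding from an adequately powered comparison. HIV incidence falls under the same claim, although an increase in the frequency of a binary response between baseline and 12 months does not describe it at all.

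**Working it through.** **Inputs.** From Sample Size and Power Calculation: 150 enrolled, 15% attrition, 80% power, two-sided 5%. Evaluable: 150 × 0.85 = 127.5, taken as 127. From Statistical Analysis: a before-after comparison, hence paired. Assumptions, because the article gives no values: within-subject correlation ρ, baseline frequency p0, the HIV-status split, and equal attrition in both strata.

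**1. The stated binary figure on the whole sample.** McNemar normal approximation for an increase d, with p1 = p0 + d:

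- p11 = p0·p1 + ρ√[p0(1−p0)p1(1−p1)], capped at p0
- ψ = p0 + p1 − 2·p11
- power = Φ{(d√n − 1.960√ψ)/√(ψ − d²)}

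With n = 127, baselines of 10, 20, 30 and 50%, and ρ from 0.2 to 0.5, 80% power is reached at 9.0 to 15.7 points. The stated 10-15 points is therefore consistent with the full evaluable sample.

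**2. What a stratum needs from a near-zero baseline.** All changes then run one way. With k changers the exact two-sided McNemar p-value is 2 × 0.5^k: 0.0625 for k = 5 and 0.031 for k = 6. So at least 6 changers are needed, and power = P(X ≥ 6), X ~ Binomial(n, d).

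- 10 points: n = 77 gives 79.4%, n = 78 gives 80.4%.
- 15 points: n = 51 gives 79.7%, n = 52 gives 81.2%.

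**3. A result that needs no assumed split.** Both strata at 10 points need 78 + 78 = 156, more than 127. At 15 points, those living with HIV must number at least 52, and 52/127 = 41%. Both strata reach 15 points only if that group is 52 to 75 of the 127 (41% to 59%).

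**4. Participants living with HIV, zero baseline, by assumed share.**

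| Share | Evaluable n | Detectable increase (points) | Power at 10 | Power at 15 |
|---|---|---|---|---|
| 15% | 19 | 38.4 | 1% | 5% |
| 24.2% | 31 | 24.3 | 8% | 32% |
| 30% | 38 | 20.0 | 18% | 52% |
| 40% | 51 | 15.1 | 40% | 80% (79.7) |
| 50% | 64 | 12.1 | 63% | 93% |

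If the baseline is not zero, the formula in step 1 with n = 31 gives 23.5 to 35 points (baselines 5-50%, ρ 0.1-0.6).

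**5. PrEP uptake.** Baseline is 0% by eligibility. At the 24.2% share, 127 − 31 = 96 HIV-negative participants are evaluable. The detectable increase is 8.1 points, and power at 10 points is 93%.

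**6. HIV incidence.** Participants at risk have no baseline frequency, and the aim is fewer infections, not an increase. None of the stated detectable effects corresponds to it.

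**7. The continuous range (secondary).** Paired detectable change in SDs = 2.802 × √[2(1−ρ)/n]. With n = 127 this is 0.352 at ρ = 0, 0.249 at ρ = 0.5 and 0.157 at ρ = 0.8. The maximum at non-negative correlation is therefore 0.35, below the stated 0.41. Covariate variance inflation could bridge the gap: (0.41/0.352)² = 1.36 and (0.53/0.352)² = 2.27 at ρ = 0, and about 2.7 and 4.6 at ρ = 0.5. No such factor is reported.

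**The case against.** The strongest reply is that the split is assumed. The 24.2% is a prevalence from a cited survey, both strata are filtered by further eligibility criteria, and a condensed article may leave stratum counts to the full protocol. This stands as a limit on the 31-participant figures. It does not touch step 3, which holds for any split, and the article makes the power claim outright instead of leaving it elsewhere.

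A second reply is that the pilot in Formative Phase saw very large effects: all HIV-negative participants engaged in PrEP, and all but one participant living with HIV became suppressed. With 31 evaluable and a zero baseline, power is 94% for 30 points. So a reader should not infer that the study is bound to miss a pilot-sized effect. What fails is the claim at 10-15 points.

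Other stronger readings are tempting but unsupported:

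- That 10-15 points needs the full sample for every outcome. PrEP uptake starts from 0%, and 52 to 78 evaluable participants suffice.
- That 15 points is out of reach at any plausible split. At a 50% share the figure from zero is 12.1.
- That 0.41-0.53 SD comes from a two-arm calculation, or that covariate adjustment cannot explain it. A paired analysis of 31 with ρ of 0.67 to 0.45 gives the same range, and the article does mention adjustment. The figures do not identify their source.
- That the detectable correlation of 0.23 is an error. It fits n = 146; 150 gives 0.227 and 127 gives 0.246. For baseline responses this is rounding, and for change scores it is minor.
- That a specific low power can be stated for incidence. Statistical Analysis specifies no incidence test or comparator rate, so any such number would belong to a design that the article does not describe.

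**Conclusion.** The power statement is wrong as written for two of the four primary outcomes and has no basis for a third. For linkage and viral suppression, 80% power at 10 points cannot coexist with the same power for the HIV-negative outcomes under any split of 127. At 15 points it requires about 41% or more of the sample to be living with HIV. Across assumed shares of 15% to 50%, the zero-baseline detectable increase runs from 38 to 12 points; at 24.2% it is about 24. These values assume an exact two-sided McNemar test, equal attrition in the strata and a near-zero baseline. At the 24.2% share, baselines of 5-50% give a similar or larger figure (23.5 to 35). For HIV incidence the claim is unsupported, which is less than saying that a specified test is underpowered. PrEP uptake meets the stated figure at the assumed split.

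The SD range is a minor inconsistency. It is conservative (at n = 127, power for 0.41 SD is at least 90% at non-negative correlation), concerns no named primary outcome, and may reflect unreported covariate inflation.

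**What to change.** Rewrite the power paragraph by HIV-status stratum. The Results section reports that enrolment is complete, so the enrolled counts are known and can replace any assumed share.

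1. For each stratum give the enrolled and expected evaluable number, the baseline frequency implied by eligibility, and the detectable change with 80% power.
2. Keep the 10-15 point claim only for outcomes and strata that meet it, and state the larger detectable change for linkage and viral suppression where they do not.
3. Withdraw the 80% power claim for HIV incidence and report incidence descriptively with a confidence interval.
4. Correct 0.41-0.53 SD, or state the sample size, correlation and variance inflation that produce it.

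The cost is text only, with no extra participants or procedures. The price is candour: the stated sensitivity for linkage and viral suppression will probably become less favourable.
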